**Table 5. Quality of TME and Pathologic Outcomes**

| Characteristics                       | Laparoscopic Surgery Group (n=XXX) | Open Surgery Group (n=XXX) | Difference,% (95% CI) | P value |
|----------------------------------------------|-------------------------------------------|-----------------------------------|------------------------------|----------------|
| Quality of TME, n (%)                 |                                           |                                   |                              | X.XX
X      |
| Complete                                     | XXX(XX.X)                                 | XXX(XX.X)                         | XX (XX.X–XX.X)               |                |
| Near-complete                                | XXX(XX.X)                                 | XXX(XX.X)                         | XX (XX.X–XX.X)               |                |
| Incomplete                                   | XXX(XX.X)                                 | XXX(XX.X)                         | XX (XX.X–XX.X)               |                |
| Quality of TME for stage I, n (%)     |                                           |                                   |                              | X.XXX          |
| Complete                                     | XXX(XX.X)                                 | XXX(XX.X)                         | XX (XX.X–XX.X)               |                |
| Near-complete                                | XXX(XX.X)                                 | XXX(XX.X)                         | XX (XX.X–XX.X)               |                |
| Incomplete                                   | XXX(XX.X)                                 | XXX(XX.X)                         | XX (XX.X– XX.X)              |                |
| Quality of TME or stage II/III, n (%) |                                           |                                   |                              | X.XXX          |
| Complete                                     | XXX(XX.X)                                 | XXX(XX.X)                         | XX (XX.X–XX.X)               |                |
| Near-complete                                | XXX(XX.X)                                 | XXX(XX.X)                         | XX (XX.X–XX.X)               |                |
| Incomplete                                   | XXX(XX.X)                                 | XXX(XX.X)                         | XX (XX.X–XX.X)               |                |
| Length of PRM, median (IQR), mm       | XX (XX.X–XX.X)                            | XX (XX.X–XX.X)                    |                              | X.XXX          |
| Overall group                                |                                           |                                   |                              |                |
| Stage I disease                              |                                           |                                   |                              |                |
| Stage II/III disease                         |                                           |                                   |                              |                |
| Length of DRM, median (IQR), mm       | XX (XX.X–XX.X)                            | XX (XX.X–XX.X)                    |                              | X.XXX          |
| Overall group                                |                                           |                                   |                              |                |
| Stage I disease                              |                                           |                                   |                              |                |
| Stage II/III disease                         |                                           |                                   |                              |                |
| Lymph nodes dissected, median (IQR)   | XX (XX.X–XX.X)                            | XX (XX.X–XX.X)                    |                              | X.XXX          |
| Overall group                                |                                           |                                   |                              |                |
| Stage I disease                              |                                           |                                   |                              |                |
| Stage II/III disease                         |                                           |                                   |                              |                |
| Negative resection margin, n (%)      |                                           |                                   |                              |                |
| Negative PRMs, No. (%)                |                                           |                                   |                              | X.XXX          |
| Overall group                                | XXX(XX.X)                                 | XXX(XX.X)                         |                              |                |
| Stage I disease                              | XXX(XX.X)                                 | XXX(XX.X)                         |                              |                |

|                                    |           |           |  |       |
|------------------------------------|-----------|-----------|--|-------|
| Stage II/III disease               | XXX(XX.X) | XXX(XX.X) |  |       |
| Negative DRMs, No. (%)      |           |           |  | X.XXX |
| Overall group                      | XXX(XX.X) | XXX(XX.X) |  |       |
| Stage I disease                    | XXX(XX.X) | XXX(XX.X) |  |       |
| Stage II/III disease               | XXX(XX.X) | XXX(XX.X) |  |       |
| Negative CRMs, No. (%)      |           |           |  | X.XXX |
| Overall group                      | XXX(XX.X) | XXX(XX.X) |  |       |
| Stage I disease                    | XXX(XX.X) | XXX(XX.X) |  |       |
| Stage II/III disease               | XXX(XX.X) | XXX(XX.X) |  |       |
| Pathologic T stage, n (%)   |           |           |  | X.XXX |
| T0/Tis                             | XXX(XX.X) | XXX(XX.X) |  |       |
| T1                                 | XXX(XX.X) | XXX(XX.X) |  |       |
| T2                                 | XXX(XX.X) | XXX(XX.X) |  |       |
| T3                                 | XXX(XX.X) | XXX(XX.X) |  |       |
| T4a                                | XXX(XX.X) | XXX(XX.X) |  |       |
| T4b                                | XXX(XX.X) | XXX(XX.X) |  |       |
| Pathologic N stage, n (%)   |           |           |  | X.XXX |
| N0                                 | XXX(XX.X) | XXX(XX.X) |  |       |
| N1a                                | XXX(XX.X) | XXX(XX.X) |  |       |
| N1b                                | XXX(XX.X) | XXX(XX.X) |  |       |
| N1c                                | XXX(XX.X) | XXX(XX.X) |  |       |
| N2a                                | XXX(XX.X) | XXX(XX.X) |  |       |
| N2b                                | XXX(XX.X) | XXX(XX.X) |  |       |
| Pathologic TNM stage, n (%) |           |           |  | X.XXX |
| 0/pCR                              | XXX(XX.X) | XXX(XX.X) |  |       |
| I                                  | XXX(XX.X) | XXX(XX.X) |  |       |
| IIA                                | XXX(XX.X) | XXX(XX.X) |  |       |
| IIB                                | XXX(XX.X) | XXX(XX.X) |  |       |
| IIC                                | XXX(XX.X) | XXX(XX.X) |  |       |
| IIIA                               | XXX(XX.X) | XXX(XX.X) |  |       |
| IIIB                               | XXX(XX.X) | XXX(XX.X) |  |       |
| IIIC                               | XXX(XX.X) | XXX(XX.X) |  |       |
| IVA                                | XXX(XX.X) | XXX(XX.X) |  |       |
| IVB                                | XXX(XX.X) | XXX(XX.X) |  |       |

**Table 6. Postoperative Recovery and Complications**

| Characteristics                                    | Laparoscopic Surgery Group (n=XXX) | Open Surgery Group (n=XXX) | Difference, % (95% CI) | P value |
|----------------------------------------------------|------------------------------------|----------------------------|------------------------|---------|
| Postoperative recovery                      |                                    |                            |                        |         |
| Time to first flatus, median (IQR), h              | XX (XX.X–XX.X)                     | XX (XX.X–XX.X)             |                        | X.XXX   |
| Time to first defecation, median (SD), h           | XX (XX.X–XX.X)                     | XX (XX.X–XX.X)             |                        | X.XXX   |
| Time to liquid diet, median (IQR), h               | XX (XX.X–XX.X)                     | XX (XX.X–XX.X)             |                        | X.XXX   |
| Time to resumption of normal diet, median (IQR), h | XX (XX.X–XX.X)                     | XX (XX.X–XX.X)             |                        | X.XXX   |
| Time to analgesic requirement, median (IQR), h     | XX (XX.X–XX.X)                     | XX (XX.X–XX.X)             |                        | X.XXX   |
| Postoperative hospital stays, median (IQR), d      | XX (XX.X–XX.X)                     | XX (XX.X–XX.X)             |                        | X.XXX   |
| Postoperative 30-day complications, n (%)   | XXX(XX.X)                          | XXX(XX.X)                  |                        | X.XXX   |
| Presacral hemorrhage                               | XXX(XX.X)                          | XXX(XX.X)                  | XX (XX.X–XX.X)         | X.XXX   |
| Active intraabdominal bleeding                     | XXX(XX.X)                          | XXX(XX.X)                  | XX (XX.X–XX.X)         | X.XXX   |
| Anastomotic bleeding                               | XXX(XX.X)                          | XXX(XX.X)                  | XX (XX.X–XX.X)         | X.XXX   |
| Anastomotic leakage                                | XXX(XX.X)                          | XXX(XX.X)                  | XX (XX.X–XX.X)         | X.XXX   |
| Chylous leakage                                    | XXX(XX.X)                          | XXX(XX.X)                  | XX (XX.X–XX.X)         | X.XXX   |
| Ileus                                              | XXX(XX.X)                          | XXX(XX.X)                  | XX (XX.X–XX.X)         | X.XXX   |
| Incision complications                             | XXX(XX.X)                          | XXX(XX.X)                  | XX (XX.X–XX.X)         | X.XXX   |
| Stoma-related complications                        | XXX(XX.X)                          | XXX(XX.X)                  | XX (XX.X–XX.X)         | X.XXX   |
| Urinary disorder                                   | XXX(XX.X)                          | XXX(XX.X)                  | XX (XX.X–XX.X)         | X.XXX   |
| Urinary tract infection                            | XXX(XX.X)                          | XXX(XX.X)                  | XX (XX.X–XX.X)         | X.XXX   |
| Cardiovascular event                               | XXX(XX.X)                          | XXX(XX.X)                  | XX (XX.X–XX.X)         | X.XXX   |
| Pneumonia                                          | XXX(XX.X)                          | XXX(XX.X)                  | XX (XX.X–XX.X)         | X.XXX   |
| ...                                                | XXX(XX.X)                          | XXX(XX.X)                  | XX (XX.X–XX.X)         | X.XXX   |
| Postoperative 30-day mortality, n (%)       | XXX(XX.X)                          | XXX(XX.X)                  | XXX(XX.X)              | X.XXX   |
| Clavien-Dindo classification                |                                    |                            |                        | X.XXX   |
| I                                                  | XXX(XX.X)                          | XXX(XX.X)                  | XX (XX.X–XX.X)         |         |
| II                                                 | XXX(XX.X)                          | XXX(XX.X)                  | XX (XX.X–XX.X)         |         |
| IIIa                                               | XXX(XX.X)                          | XXX(XX.X)                  | XX (XX.X–XX.X)         |         |
| IIIb                                               | XXX(XX.X)                          | XXX(XX.X)                  | XX (XX.X–XX.X)         |         |
| IVa                                                | XXX(XX.X)                          | XXX(XX.X)                  | XX (XX.X–XX.X)         |         |
| IVb                                                | XXX(XX.X)                          | XXX(XX.X)                  | XX (XX.X–XX.X)         |         |

|   |           |           |                |  |
|---|-----------|-----------|----------------|--|
| V | XXX(XX.X) | XXX(XX.X) | XX (XX.X–XX.X) |  |
|---|-----------|-----------|----------------|--|

**Table 7. The DFS (mon) for Laparoscopic Surgery vs Open Surgery within 3 Years after Surgery (mITT)**

|                    | Laparoscopic Surgery Group | Open Surgery Group | P value |
|--------------------|-----------------------------------|---------------------------|-----------------------|
| N           | XXX                               | XXX                       | X.XXX                 |
| Censored(%) | XX(XX.X)                          | XX(XX.X)                  |                       |
| Events(%)   | XX(XX.X)                          | XX(XX.X)                  |                       |
| 25%(95%CI)  | XX.X (XX.X~XX.X)                  | XX.X (XX.X~XX.X)          |                       |
| 50%(95%CI)  | XX.X (XX.X~XX.X)                  | XX.X (XX.X~XX.X)          |                       |
| 75%(95%CI)  | XX.X (XX.X~XX.X)                  | XX.X (XX.X~XX.X)          |                       |

**Table 8. The DFS (mon) for Laparoscopic Surgery vs Open Surgery within 3 Years after Surgery (PPS)**

|                    | Laparoscopic Surgery Group | Open Surgery Group | P value |
|--------------------|-----------------------------------|---------------------------|-----------------------|
| N           | XXX                               | XXX                       | X.XXX                 |
| Censored(%) | XX(XX.X)                          | XX(XX.X)                  |                       |
| Events(%)   | XX(XX.X)                          | XX(XX.X)                  |                       |
| 25%(95%CI)  | XX.X (XX.X~XX.X)                  | XX.X (XX.X~XX.X)          |                       |
| 50%(95%CI)  | XX.X (XX.X~XX.X)                  | XX.X (XX.X~XX.X)          |                       |
| 75%(95%CI)  | XX.X (XX.X~XX.X)                  | XX.X (XX.X~XX.X)          |                       |

**Figure 1.** Kaplan–Meier curve for comparison of 3-year DFS rate between two groups (mITT)

**Figure 2.** Kaplan–Meier curve for comparison of 3-year DFS rate between two groups (PPS)

**Table 9. Cox Regression Model Analysis of DFS (mITT)**

|               |                                      | DF | HR | 95%CIL | 95%CIU | P value |
|---------------|--------------------------------------|-----------|-----------|---------------|---------------|----------------|
| Group  | Laparoscopic Surgery vs Open Surgery | X         | X.XX      | X.XX          | X.XX          | X.XXX          |
| Center | Center 1 vs Center X                 | X         | X.XX      | X.XX          | X.XX          | X.XXX          |
|               | Center 2 vs Center X                 | X         | X.XX      | X.XX          | X.XX          | X.XXX          |
|               | Center...vs Center X                 | X         | X.XX      | X.XX          | X.XX          | X.XXX          |
| XXX    |                                      | X         | X.XX      | X.XX          | X.XX          | X.XXX          |

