## 8 Statistical analyses

### 8.1 Sample size estimation

The sample size was estimated using a log-rank test based on a 3-year DFS with a noninferiority margin of 10%. At the time of this trial design, a noninferiority margin of 10% was determined to be clinically acceptable. Considering distinct prognoses in patients with stage I versus II/III disease, the sample size was calculated separately. Assumptions for the 3-year DFS rate in the open surgery group were 94.3% and 75.2% for clinical stage I and II/III diseases, respectively, with 359 patients with stage I disease (laparoscopic 240, open 119), 609 patients with stage II/III disease (laparoscopic 406, open 203), and a total of 968 patients (laparoscopic 646, open 322) were required to provide an 80% power with a one-sided  $\alpha$  of 2.5%. One thousand sixty-five patients were aimed to enroll to allow for exclusions after

randomization to maintain the required statistical power. All calculations allowed for a 20% dropout. The planned and follow-up period were three years and five years, respectively.

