## **8.2 Analysis datasets**

**(1) Modified intention-to-treat (mITT):** The mITT population is defined as all randomized subjects except those excluded after randomization. The modified intention-to-treat (mITT) population will serve as the primary population for efficacy analyses in this study.

**(2) Per-protocol set (PPS):** The PPS includes patients who underwent the assigned surgery only. In other words, the participants who meet the trial plan, have good compliance, and complete the items specified in the eCRF are included in the per-protocol (PP) analysis. PP analysis is mainly applied to the primary outcome measure.

**(3) Safety set (SS):** The SS includes the actual data of participants who have received treatment and have records of safety indicators. The missing data of safety indicators cannot be obtained from carry-over from previous records. The dataset includes some patients excluded from the trial, e.g., those whose age exceeds the inclusion criteria. The incidence of adverse reactions is determined by using the number of cases in the SS as a denominator.

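### The per-protocol tables for DFS carry no between-arm estimate with a confidence limit, so as laid out they cannot show whether a 10-point deficit is excluded

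*Combined protocol and SAP*

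**What the plan says.** SAP 8.2 makes mITT the primary efficacy population and adds a per-protocol set, of which it says: "PP analysis is mainly applied to the primary outcome measure". Protocol 12.1 gives the PPS the same role.

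SAP 8.1 sets the margin: "The sample size was estimated using a log-rank test based on a 3-year DFS with a noninferiority margin of 10" (per cent). It assumes open-arm 3-year DFS of "94.3% and 75.2% for clinical stage I and II/III diseases, respectively". No hazard-ratio margin is stated.

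For the primary outcome, SAP 8.3.3 lists Kaplan-Meier estimation, a log-rank test, a Cox hazard ratio with a one-sided 95% interval, and a decision against prespecified noninferiority criteria. It ties none of these to an analysis set. It does not say how the PPS result bears on the conclusion.

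SAP 9 shows proposed output. Among the DFS shells:

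- Table 7 and Figure 1 are for mITT.
- "Table 8. The DFS (mon) for Laparoscopic Surgery vs Open Surgery within 3 Years after Surgery (PPS" and Figure 2 are their PPS counterparts.
- The Cox shell, "Table 9. Cox Regression Model Analysis of DFS (mITT", has no PPS counterpart.

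**The concern.** A per-protocol analysis is useful in a noninferiority trial because departures from the assigned operation can bring the mITT arms together. To serve that purpose it has to answer the same question as the main analysis, namely whether a deficit as large as the margin is excluded. A P value for equality of two curves does not answer it. A non-significant result is compatible both with no difference and with a deficit of 10 points.

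If only Table 8 and Figure 2 are produced, readers get a PPS result that cannot be set against the margin. In an open-label trial it is better not to leave until results are known whether a PPS effect estimate is reported.

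**Working it through.** **1. The DFS shells side by side**

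| Output | mITT | PPS |
|---|---|---|
| Counts, quantiles with per-arm CIs, one P value | Table 7 | Table 8 |
| Kaplan-Meier curve | Figure 1 | Figure 2 |
| Cox hazard ratio with 95% limits | Table 9 | none |
| 3-year DFS difference with a limit | none | none |

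The P value in Table 8 is unlabelled. The log-rank test is the two-group test that SAP 8.3.3 names alongside Cox, so it is the natural reading.

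**2. The plan's figures.** The group totals add up: 240 + 119 = 359, 406 + 203 = 609 and 359 + 609 = 968. The enrolment target follows from 968 × 1.10 = 1064.8, or 1065. This point disputes none of them.

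**3. Do the quantiles help?** Under exponential DFS with 3-year rate S, DFS falls to 75% at t = 3 × ln(0.75) / ln(S) years.

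- Stage II/III (S = 0.752): 3.03 years; the median is 7.3 years.
- Stage I (S = 0.943): 14.7 years.
- Pooled, S = (359 × 0.943 + 609 × 0.752) / 968 = 0.823: 4.4 years.

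At the planned rates essentially no quantile is reached inside Table 8's 3-year window. The P value and the curve are then the only comparative content.

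**4. How far apart are non-significance and noninferiority?** Assume proportional hazards, the planned numbers with no PPS exclusions or losses, and 3-year events at the open-arm rates.

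- Margin as a hazard ratio: ln(S − 0.10) / ln(S). Stage II/III: ln(0.652) / ln(0.752) = 1.50. Stage I: ln(0.843) / ln(0.943) = 2.91.
- Events: 609 × 0.248 = 151.0 and 359 × 0.057 = 20.5.
- SE of log HR at 2:1: 1 / √(events × 2/9) = 0.173 and 0.469.
- Noninferiority at one-sided 97.5% needs an observed HR below margin × exp(−1.96 × SE): 1.07 and 1.16.
- Two-sided P < 0.05 against laparoscopy needs an observed HR above exp(1.96 × SE): 1.40 and 2.51.

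Between 1.07 and 1.40 in stage II/III, and between 1.16 and 2.51 in stage I, P is non-significant and noninferiority is not shown. For example, an observed HR of 1.25 in stage II/III gives z = ln(1.25) / 0.173 = 1.29 and P = 0.20. The upper limit is 1.25 × exp(1.96 × 0.173) = 1.75, well above 1.50.

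**5. How often would this happen?** The simulation assumes exponential DFS by stage at the planned rates, with the deficit subtracted in the laparoscopic arm of each stage. It uses the planned stage mix, 2:1 allocation, 20% exponential loss over 3 years and data cut at 36 months. The 3-year difference is Kaplan-Meier with Greenwood variance. The documents give no PPS size. It is assumed to be 80-90% of 968 (774 to 871), with 959 (90% of 1065) as a larger case.

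| True deficit | Log-rank P > 0.05 (774-871) | 97.5% limit excludes −10 points (774-871) | P > 0.05, noninferiority not shown (774-871) | The same, PPS of 959 |
|---|---|---|---|---|
| 5 points | 65-67% | 34-38% | 27-34% | 19% |
| 7 points | 38-44% | about 15% | 24-30% | 15% |
| 10 points | 11-16% | 2-3% | 10-14% | 8% |

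With 2,000 trials a proportion near 30% has a standard error of √(0.3 × 0.7 / 2000), about 1 point. A 4,000-trial repeat gave 26-34%, 24-31% and 9-13% for the fourth column, and 20%, 17% and 7% for the last. The figures are good to about two points.

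**The case against.** The strongest reply is that table shells are not the analysis plan. SAP 8.2 directs the per-protocol analysis to the primary outcome. SAP 8.3.3 prescribes Cox and the noninferiority decision for that outcome without restricting them to mITT. SAP 9 is headed as a proposed publication format and is plainly incomplete: quality of life, bladder and sexual function are prespecified but have no shell. A missing shell does not prove a missing analysis.

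Much of this stands. A reader might infer that the plan rules out a PPS effect estimate; the documents do not say so. But nothing requires one either, and the mITT label on the only Cox shell, beside the paired DFS tables and figures, points the other way. Even on the generous reading, a PPS hazard ratio would not meet the margin as stated, because the margin is an absolute 10 points with no hazard-ratio equivalent.

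Two further points are fair. Table 9 is not the only shell with confidence intervals: Table 8 has them for per-arm quantiles, and Tables 5 and 6 have them for differences in other outcomes. It is the only one with a between-arm interval for DFS. Also, the PPS need not be the conservative set. The SAP limits it to patients who had only the assigned surgery, and conversion occurs only in the laparoscopic arm. If converted patients are left out, that arm alone loses them.

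**Conclusion.** The point holds in limited form. The PPS output as laid out cannot show whether a 10-point DFS deficit is excluded, and the text does not explicitly supply what the shells lack. The primary decision rests on mITT and is not affected, so this is a cheap improvement, not a flaw in the main analysis.

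At true deficits of 5, 7 and 10 points, the PPS would give P > 0.05 without noninferiority shown in about 27-34%, 24-30% and 10-14% of trials, or about 19%, 15% and 8% with a PPS of 959. These rates depend on the assumed PPS size, exponential DFS and loss pattern. They model no crossover, so they do not measure how far mITT might be diluted.

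A reader might divide 11-16% by 2-3% at a true 10-point deficit and call the result a false-reassurance ratio. The documents do not support that. No section says that P > 0.05 in the PPS will be read as agreement with mITT, and SAP 8.3.3 refers the decision to noninferiority criteria. At that deficit the log-rank test would in fact be significant in most trials.

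**What to change.** - **SAP 8.3.3:** state that the primary DFS analysis is reported for mITT and also for the PPS.
- **Table 8:** add Kaplan-Meier 3-year DFS per arm and the laparoscopic-minus-open difference. Give it a one-sided 97.5% limit (the lower end of a two-sided 95% interval), which matches the one-sided 2.5% alpha in SAP 8.1, and compare it with the 10-point margin.
- **Table 7:** add the same rows for mITT, since no mITT shell shows this difference either.
- **Table 9:** add a PPS copy as support. On its own it would not be enough, because the margin is not on the hazard-ratio scale.
- **Interpretation:** state that the PPS result is read from that limit and not from the log-rank P value, and that it is supportive because the PPS is not necessarily the conservative set.

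The cost is SAP wording, a few rows and one extra table from data already held. The downside is that the PPS limit may visibly fail to exclude the margin when the mITT limit does.
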